## Abstract

**Background:**

Light information is the most important cue of circadian rhythm which synchronizes biological rhythm with external environment. Circadian misalignment of biological rhythm and external environment is associated with increased risk of depression, insomnia, obesity, diabetes, cardiovascular disease, and cancer.

Increased light transmission by cataract surgery may improve circadian misalignment and related health outcomes. Although some observational studies have shown improvement of depression and insomnia after cataract surgery, randomized controlled trials are lacking. We will conduct a parallel-group, assessor-blinded, simple randomized controlled study comparing a cataract surgery group at three months after surgery with a control group to determine whether cataract surgery improves depressive symptoms, sleep quality, body mass regulation, and glucose and lipid metabolism.

**Methods/Design:**

We will recruit patients who are aged 60 years and over, scheduled to receive their first cataract surgery, and have grade 2 or higher nuclear opacification as defined by the lens opacities classification system III. Exclusion criteria will be patients with major depression, severe corneal opacity, severe glaucoma, vitreous haemorrhage, proliferative diabetic retinopathy, macular oedema, age-related macular degeneration, and patients needing immediate or combined cataract surgery. After baseline participants will be randomized to two groups. Outcomes will be measured at three months after surgery among the intervention group, and three months after baseline among the control group. We will assess depressive symptoms as a primary outcome, using the short version geriatric depression scale (GDS-15). Secondary outcomes will be subjective and actigraph-measured sleep quality, sleepiness, glycated haemoglobin, fasting plasma glucose and triglyceride, low-density lipoprotein cholesterol, high-density lipoprotein cholesterol, body mass index, abdominal circumference, circadian rhythms of physical activity and wrist skin temperature, and urinary melatonin metabolite. Chronotype and visual function will be assessed using the ‘morningness-eveningness’ questionnaire, the Munich chronotype questionnaire, and the National Eye Institute Visual Function Questionnaire.

**Discussion:**

Although there are potential limitations due to the difference in duration from baseline survey to outcome measurements between two groups, any seasonal effect on the outcome measurement will be balanced as a result of continuous inclusion of participants through the year, and outcomes will be adjusted for day length at outcome measurements at analysis.

**Trial registration:**

UMIN000014559, UMIN Clinical Trials Registry, registered on 15 July 2014.

## Background

Light information is the dominant stimulus synchronising the master internal biological clock at the suprachiasmatic nuclei (SCN) with the external environment. The internal biological rhythm of humans is close to that of the earth’s rotation, according to a study of the rhythm of core body temperature independent of the external environment
[1]. The misalignment of biological rhythm and external environment is associated with many health problems. Epidemiological studies among shift workers suggest that circadian misalignment is significantly associated with an increased risk of sleep disturbance
[2], depression
[3], obesity and metabolic syndrome
[4, 5], diabetes
[6, 7], ischaemic heart disease
[8, 9], and stroke
[10]. Light information modifies the timing of the internal biological rhythm according to the phase response curve to light
[11]. Light exposure in the early morning (after core body temperature minimum) is responsible for the subsequent phase advance in melatonin secretion; in contrast, light in the evening (before core body temperature minimum) is responsible for the subsequent phase delay. Simultaneously, the amplitude of the internal biological rhythm is modified by light information
[12].

In contrast to visual light information received by rod and cone cells of the retina and transmitted via the optic nerve, non-visual light information is mainly perceived by recently discovered intrinsically photosensitive retinal ganglion cells (ipRGCs), which contain melanopsin, and are transmitted to the SCN via the retinohypothalamic tract (RHT)
[13]. The action spectrum for melatonin suppression among humans show a peak at a shorter wavelength (464 nm) than that for visual information (approximately 555 nm)
[14].

Cataracts are a prevalent cause of visual impairment and a leading cause of blindness worldwide. The World Health Organisation reported that 33% of visual impairment (representing 95 million people) and 51% of blindness (representing 19.9 million people) are due to cataracts
[15]. Among age-related cataract patients, the light transmission at the most sensitive spectrum for the photic entrainment of internal biological rhythms decreases from 82% at 10 years to 23% at 80 years
[16]. Circadian misalignment because of the decreased input of light information caused by cataracts may explain the higher prevalence of depression among cataract patients
[17], and the association of decreased light transmission by lens yellowing with sleep disturbance
[18].

The research hypothesis of the present study is that cataract surgery, which removes the clouded lens and implants an artificial intraocular lens (IOL), will increase the input of non-visual light information and improve circadian alignment and its related health outcomes, such as depression, sleep disturbances, body mass regulation, and glucose and lipid metabolism
[19].

The hypothesis is supported by studies of bright light intervention and light exposure in real-life situations. A Cochrane systematic review showed a significant reduction of depressive symptoms (standardised mean difference −0.20, 95% CI −0.38 to −0.01) from a meta-analysis of 18 randomized controlled trials (RCTs) among 505 patients with non-seasonal depression
[20], and another systematic review also revealed the significant effectiveness of bright light intervention and light exposure among seasonal affective disorders (eight RCTs totalling 132 patients)
[21]. In addition, recent RCTs have revealed the effectiveness of bright light therapy on depression, accompanied by improved sleep quality and internal biological rhythm. Bright light therapy (pale blue light at 7,500 lux for one hour) significantly decreased depressive symptoms compared with the placebo control group (red dim light at 50 lux) among 89 patients with non-seasonal depression, and was accompanied by an increase in salivary melatonin in the evening and better actigraph-measured sleep parameters
[22, 23]. An intervention to increase light exposure by installing a ceiling light in the shared living room in group care facilities significantly decreased depressive symptoms, and increased total sleep time, as assessed by an actigraph, among elderly participants. In addition, a significant interaction of light intervention and melatonin administration on sleep efficiency was observed
[24]. Higher daylight exposure increases melatonin secretion at night, according to an interventional study
[25] and our population-based observational study
[26].

Short-term and long-term influence of cataract surgery on depression and subjective sleep quality have been reported by some observational studies. Compared with depressive symptoms assessed before cataract surgery, significant decreases in depressive symptoms have reported at two months
[27, 28], three months
[29], and one year
[30] after surgery. In addition, improved subjective sleep quality was reported at one month
[31], two months
[32, 33], and nine months
[34] after surgery. However, evidence from RCTs on the effect of cataract surgery on depressive symptoms, sleep disturbance, and internal biological rhythms is lacking.

In contrast to bright light therapy conducted during the daytime, cataract surgery may increase the input of light information, not only in the daytime, but also during the night-time. Increased input of light information during the night-time may be deleterious to health outcomes. Indeed, we found significant cross-sectional association of increased light at night with increased prevalence of obesity, dyslipidaemia
[35], sleep disturbance
[36], and depression
[37] in real-life situations among elderly individuals. These associations are supported by previous experimental evidence
[38–40].

Here, we will conduct a parallel-group, assessor-blinded, simple RCT comparing the intervention group at three months after surgery with the control group at three months after baseline, to determine whether cataract surgery modifies the internal biological rhythm and improves its related health outcomes such as depression, sleep quality, body mass regulation, and glucose and lipid metabolism.

## Methods/Design

All intervention processes associated with the present study are conducted at Nara Medical University hospital. The protocol of this study has been registered at the University Hospital Medical Information Network Clinical Trials Registry (UMIN-CTR, identifier: UMIN000014559). The CLOCK-IOL (Cataract Surgery and Circadian Biological Rhythm among Japanese Older People with Cataract in Nara, Kansai Region: Influence of Intra Ocular Lens Implantation) study was approved by the institutional review board of Nara Medical University (approval number: 13-032). This research complies with the Declaration of Helsinki. Before enrolment to this study, we will obtain written informed consent from all participants.

We will include participants continuously through the year with similar speed, and inclusion of the present study will finish at the same date as the started year. After baseline measurements, all participants will be randomly allocated to either the intervention group or the control group in a 1:1 ratio without restrictions such as blocking and stratification. The outcomes among the intervention group will be measured at three months after surgery. Among the control group, the outcomes will be measured at three months after baseline. The control group will receive delayed cataract surgery shortly after the outcome measurement (Figure 
1).

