### Patients of cataract surgery for both eyes

We include participants undergoing cataract surgery for single and both eyes. The surgery for both eyes among the intervention group will be completed within the same time-scale, one to two weeks, and the same kind of IOLs will be used for both eyes. Outcomes will be measured at three months after the latest surgery.

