### Statistical analysis

We will compare the outcomes between the control group and the intervention group based on the intention-to-treat principle. For missing values due to loss to follow-up after baseline measurement, we will impute baseline data using the last observation carried forward (LOCF) method. For continuous variables with normal distributions, the mean and standard deviation will be reported. For variables not distributed normally, the median and interquartile range will be reported. Means, medians, and proportions will be compared using the t test, the Mann-Whitney U test, and the χ^2^ test, respectively. We will use analysis of covariance to estimate adjusted mean values and 95% CIs. The prevalence of the two groups will be tested using multivariate logistic regression analysis. To assess the phase, amplitude, and robustness of the circadian rhythm, we will use the cosinor model
[69], the sigmoidally transformed cosine model
[70], and the generalised additive model
[71]. We will conduct a subgroup analysis at baseline according to the severity of cataract and chronotype.

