## Discussion

To conduct an RCT assessing the long-term effect of cataract surgery is ethically difficult, because the effectiveness of cataract surgery for visual acuity is established. To assess the effect of cataract surgery after three months with minimum disadvantage to the control group due to delayed surgery, we have potential limitations due to the difference of duration from baseline survey to outcome measurements between the two groups. Compared with the control group, the intervention group will spend a longer time from baseline measurement to outcome measurement due to the duration between baseline and surgery, and it may distort the results because of a seasonal effect on outcomes. However, we will continuously include participants with a similar speed though the year, and will finish this study at the same date as started in the previous year. As a result, the number of overestimated outcomes and underestimated outcomes due to the seasonal influence will be balanced between the two groups. In the statistical analysis, we will compare the outcomes adjusted for seasonal variables, such as day length at outcome measurement, using ANOVA for continuous variables and multivariate logistic regression analysis for categorical outcomes.

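### Outcomes are timed from surgery in one arm and from baseline in the other, so change over the pre-surgery wait is confounded with arm and unoperated intervention patients have no outcome date

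*Protocol article*

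**What the plan says.** Methods/Design in the protocol article sets the order of events: "After baseline measurements, all participants will be randomly allocated to either the intervention group or the control group in a 1:1 ratio". Baseline is therefore a starting point that both arms share. The same section then sets two different clocks. For the intervention arm: "The outcomes among the intervention group will be measured at three months after surgery". For controls: "Among the control group, the outcomes will be measured at three months after baseline". The Abstract and Background repeat both anchors.

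The section on patients having surgery on both eyes moves the intervention clock again: "Outcomes will be measured at three months after the latest surgery". On the gap between operations it says: "The surgery for both eyes among the intervention group will be completed within the same time-scale, one to two weeks".

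The Primary outcome section lists the change in GDS-15 from baseline, described as a three-month change, among the quantities compared between arms.

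The Discussion concedes that "the intervention group will spend a longer time from baseline measurement to outcome measurement due to the duration between baseline and surgery". It explains that the design studies the three-month effect of surgery while keeping the disadvantage of delay to controls small. Its remedy is even recruitment over a full year and covariate adjustment: "we will compare the outcomes adjusted for seasonal variables, such as day length at outcome measurement".

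The Statistical analysis section says: "We will compare the outcomes between the control group and the intervention group based on the intention-to-treat principle". It carries baseline values forward when data are missing because of loss to follow-up.

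**The concern.** Randomisation makes the arms comparable at the same time after allocation. Here the intervention arm is always measured later. If GDS-15, weight or HbA1c would drift with time whatever the treatment, the drift over the extra weeks enters the difference between arms and cannot be told apart from an effect of surgery. The change score is affected directly, because it is described as a three-month change but covers more than three months in the intervention arm.

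The second issue is the patient allocated to surgery who cancels or defers it but keeps attending. An outcome date defined by surgery does not exist for that patient, yet an intention-to-treat comparison needs an outcome from everyone randomised. At stake is whether a difference, or its absence, can be credited to surgery.

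**Working it through.** **Inputs from the protocol article**
- Control interval: 3 months from baseline, about 13 weeks (Methods/Design).
- Intervention interval: 3 months from the latest surgery (Methods/Design; Patients of cataract surgery for both eyes).
- Second eye: 1 to 2 weeks.
- Wait from baseline to first surgery: not given, and no limit stated.
- 20.0% prevalence, 7-point target difference, 475 per group, 1,000 in total (Sample size).

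**Plan's own figure.** The protocol gives no interval to reproduce. The sample size is roughly reproduced: 20% against 13%, two-sided 5%, 80% power gives 469 per group with continuity correction (441 without), against the stated 475. Then 475 / 0.95 = 500 per group, or 1,000 in total. None of this depends on when outcomes are measured.

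**Difference in interval.** Let w be the wait in weeks and s the second-eye gap (0 for one eye, at most 2 for two).
- Control = 13
- Intervention = 13 + w + s
- Difference = w + s

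| Assumed w | Intervention interval, s = 0 to 2 | Difference |
|---|---|---|
| 2 | 15 to 17 weeks | 2 to 4 weeks |
| 4 | 17 to 19 weeks | 4 to 6 weeks |
| 8 | 21 to 23 weeks | 8 to 10 weeks |
| 12 | 25 to 27 weeks | 12 to 14 weeks |

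**What season adjustment covers.** Even recruitment over a full year would largely balance a purely seasonal shift, because patients enter at every point of the cycle. It does not balance elapsed time, because the extra interval always falls in the same arm. Day length at outcome is a function of calendar date, not of weeks since baseline. Adding elapsed time as a covariate would not separate the two cleanly either: the interval is fixed by design in controls, so it is almost determined by arm.

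**What a shift would do, if there were one.** Suppose surgery has no effect and elapsed time alone lowers prevalence in the intervention arm from 20% by b. With n = 475 per arm, mean prevalence p̄ = 0.20 − b/2, SE0 = √(2p̄(1−p̄)/n) and SE1 = √((p1(1−p1)+p2(1−p2))/n):

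P(reject) = 1 − Φ((1.96·SE0 − b)/SE1) + Φ((−1.96·SE0 − b)/SE1)

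- b = 1 point: 6.7%
- b = 2 points: 12.3%
- b = 3 points: 22.1%

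The nominal level is 5%. The values of b are assumptions that show sensitivity only. The document supports no particular value and no direction.

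**Patients not operated on.** Set the two rules side by side. The outcome date is three months after surgery, and without surgery there is no date. The carry-forward rule is for loss to follow-up, and a patient who still attends is not lost. Neither rule clearly says when, or whether, this patient's outcome is measured.

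**The case against.** The strongest reply is that this is a disclosed and reasoned trade-off. The Discussion names the unequal interval and gives its reason. Controls have their own surgery shortly after their outcome visit, so a later control visit would delay that surgery, which the design tries to keep short. This stands. It rules out moving the control visit later as the simple remedy, and it makes the point a residual weakness rather than a hidden error.

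It is also fair to say that the size is entirely assumed. With a short wait and little drift the bias would be a small fraction of the 7-point target.

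Three stronger readings are tempting but unsupported:
- A reader might infer that all change since baseline is confounded with arm. The first three months are common to both; only the extra wait differs.
- A reader might infer that randomisation no longer protects the trial. Allocation is central and concealed, so the groups are still comparable at baseline.
- A reader might infer that unoperated patients are assigned zero change and that intention-to-treat is impossible. The carry-forward rule is limited to loss to follow-up, and a patient with baseline carried forward would still be analysed in the allocated arm.

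The full protocol may contain a visit rule for unoperated patients that a condensed article omits. The outcome anchor, however, is stated here, and the gap follows from it. What the reply does not meet is that the Discussion's defence addresses season and nothing else.

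**Conclusion.** The point holds in limited form. As written, the intervention arm is measured systematically later after baseline than the control arm, by the wait for surgery plus up to 2 weeks for a second eye. Change over that extra time is confounded with arm, and neither year-round recruitment nor day-length adjustment removes it.

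The difference is about 2 to 14 weeks if the wait is 2 to 12 weeks, which is an assumption. The resulting bias cannot be computed, because the document gives neither the wait nor any drift over time. It may be small, but nothing stated in the article keeps it so.

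The outcome date for intervention patients who attend but are not operated on is undefined, which fits poorly with the intention-to-treat statement without making it unworkable. This is a cheap improvement worth making before recruitment, not evidence that the comparison is invalid.

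**What to change.** - Book baseline measurement and randomisation as close as practicable to the scheduled surgery date, so that the intervals nearly match. Participants must already be scheduled for surgery to be eligible.
- At randomisation, fix each intervention patient's outcome visit at three months from the scheduled surgery date (the second-eye date if both eyes are planned). Hold that visit whether or not surgery took place.
- Report days from baseline to outcome by arm.
- Reword the Discussion to say that season adjustment does not remove effects of elapsed time.

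The Trial status section says recruitment had not started, so this means changes to wording and scheduling. The sample size stays at 475 per group and 1,000 in total, and control follow-up is not lengthened.

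The cost is tighter booking before surgery, and a firm date, including any second-eye date, must be on record at randomisation. A patient whose surgery slips will be measured less than three months after it, so days since surgery should be recorded as well. Any change to the timing of the control group's own surgery is for the investigators to settle.

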**Figure 1 Fig1:**
[figure not shown]
**Flow chart of participants.**

### Participants

We will assess the eligibility of patients in Nara Medical University Hospital who have been diagnosed as having cataracts according to the following inclusion and exclusion criteria.

#### Inclusion criteria

The inclusion criteria for this study are as follows:Patients scheduled for their first cataract surgery,Aged 60 years or over, andDiagnosed with cataracts of grade 2 nuclear opacification as defined by the lens opacities classification system III [41].

#### Exclusion criteria

The exclusion criteria for this study are as follows:Major depression with current therapy,Severe mental illness or dementia,Severe corneal opacities with difficulty in assessment of lens opacity or fundal examination,Glaucoma with a visual field deficit of at least mean deviation >14 dB (Humphrey perimeter),Vitreous haemorrhage,Proliferative diabetic retinopathy,Macular edema,Age-related macular degeneration,Patients needing immediate cataract surgery, orPatients needing combined cataract and glaucoma surgery or combined cataract surgery and vitrectomy.

### Intervention

Before the cataract surgery, the axial length of the eye will be measured with an A-scan UD-6000 (Tomey, Nagoya, Japan). Yellow aspherical IOL (SN60WF, Alcon, Fort Worth, Texas, United States), yellow spherical IOL (SN60AT, Alcon, Fort Worth, Texas, United States), or clear spherical IOL (SA60AT, Alcon, Fort Worth, Texas, United States) will be used for the cataract surgery. The appropriate power of the IOL will be estimated using the SRK/T formula for each IOL
[42]. The kind of IOL used for the cataract surgery was randomly allocated to yellow spherical IOL, yellow aspherical IOL, or clear spherical IOL in a 1:1:2 ratio. After phacoemulsification with a small incision, IOL will be implanted.

